## Methods/design

### Study design

The REPEAT trial is a Dutch multicentre, phase II, single-arm prospective study at the Amsterdam University Medical Center (UMC) and Catharina Hospital Eindhoven in the Netherlands. The trial started in both centres in January 2025 and the estimated end date is December 2032. Eligible patients will be treated with ablative single-dose PBI followed by BCS after 3 (±one) weeks. At baseline (prior to RT) and prior to BCS, toxicity, PROMs and cosmetic outcome will be assessed. Additionally, a preoperative MRI will be performed 3 (±one) weeks following RT to evaluate the acute tumour response. The primary objective is to assess the feasibility of single-dose preoperative PBI and second BCS for an IRBE after previous BCT based on acute toxicity. The secondary objectives are to assess treatment-induced toxicity, radiological and pathological response, mastectomy rate, PROMs, cosmetic results, patient comfort during RT treatment delivery, oncological outcomes and RT-associated immune response markers (CD4, CD8 and FOXP3 expressing T cells) in blood and tumour tissue. All tumour tissue and blood samples of patients will be preserved at the Amsterdam UMC Central Biobank, location Vrije Universiteit Medical Center. This study design is based on the ABLATIVE study in patients with primary low-risk breast cancer, but with a shorter interval between RT and BCS (NCT05350722).^14 15^

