### Study population

The study population will consist of women who are 50 years or older with a low-risk IRBE after previous BCT. The definition of low-risk IRBE is based on the ASTRO suitable criteria for PBI.^1^ Patients are eligible for study participation in case of: tumour size ≤2 cm on MRI, unifocal non-lobular invasive carcinoma, Bloom-Richardson grade 1 or 2, ER-positive and HER2-negative, clinical node negative on 18F-fluorodeoxyglucose positron emission tomography computed tomography (FDG PET-CT)/ultrasound/MRI, no distant metastases and no or mild late toxicity (no grade 2 or higher) from previous BCT. The inclusion and exclusion criteria are presented in table 1.

**Table 1 T1:** Inclusion and exclusion criteria

Inclusion criteria	Exclusion criteria
WHO performance status 0–2	Ipsilateral invasive breast cancer event <2 years after first breast-conserving therapy for breast cancer
Women ≥50 years with an ipsilateral invasive recurrent breast cancer event after previous breast-conserving surgery and postoperative whole breast irradiation	Other malignancy within 5 years before ipsilateral breast recurrence diagnosis. For carcinoma in situ, no specific time span to ipsilateral breast recurrence diagnosis is required for inclusion
Tumour size ≤2 cm and unifocal on MRI	Known breast cancer mutation gene carrier
Tumour histology as assessed on biopsy: Bloom-Richardson grade 1 or 2 Non-lobular invasive histological type carcinoma Oestrogen receptor positive HER2 receptor negative No lymphovascular invasion	Collagen synthesis disease (eg,osteogenesis imperfecta, Ehlers-Danlos syndrome, systemic sclerosis)
	Delayed wound healing after primary treatment
No extensive DCIS (outside tumour size of 2 cm) on mammography or tumour biopsy, including non-mass enhancement on MRI	Previous ipsilateral mastectomy
Clinical node negative on 18-F FDG PET-CT, ultrasound and MRI	Invasive lobular carcinoma or DCIS without invasive cancer
No distant metastasis	MRI absolute contraindications and intolerance
No or mild late toxicity (no grade 2 or higher) from previous breast-conserving therapy	Indication for treatment with neoadjuvant chemotherapy
Adequate understanding of the Dutch language	Legal incapacity
	Poor cosmetic outcome after initial breast-conserving therapy

DCIS, ductal carcinoma in situ; FDG PET-CT, fluorodeoxyglucose positron emission tomography computed tomography; HER2, human epidermal growth factor receptor 2.

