### Study outcomes

The primary endpoint is the rate of acute ≥grade 2 treatment-induced toxicity within 3 months following preoperative RT, using the Common Terminology Criteria for Adverse Events (CTCAE) V.0 (skin toxicity, breast oedema, breast pain and chest wall pain) and the Clavien-Dindo classification (wound infection). Secondary endpoints are any acute (including grade 1) and late treatment-induced toxicity according to CTCAE V.5.0 and the Clavien-Dindo classification. Radiological response will be assessed using a breast MRI, 3 weeks after RT (preoperatively). Pathological response will be evaluated in the resection specimen. In addition, the mastectomy rate will be assessed 5 years after BCS. PROMs will be evaluated using the European Organization for Research and Treatment of Cancer core-30 and breast cancer-specific questionnaires. Cosmetic outcome will be assessed by the patients using the BREAST-Q questionnaire. The physician will score cosmetic outcome as excellent, good, fair or poor based on changes in breast appearance. Additionally, cosmetic outcome will be evaluated objectively using digital photographs analysed by the BCCT.core software and 3D Vectra XT software. Oncological outcomes will be assessed by evaluating local, regional and distant event rates, and disease-free, breast cancer-specific survival (BCSS) and OS. Disease-free survival is defined from the date of RT to the date of local, regional or distant recurrence. BCSS and OS will be determined from the date of RT to the date of death caused by breast cancer and any cause, respectively. RT-associated (immune-activation/-suppressor) biomarkers in blood and tumour tissue will be explored. An overview of the time points at which the outcomes are assessed is shown in figure 1.

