### Statistical analysis

The sample size calculation is based on the primary endpoint of the rate of grade 2 or higher acute treatment-associated toxicity within 90 days (skin toxicity, breast oedema, breast pain, chest wall pain, wound infection). We expect that 30% of our patients will experience ≥grade 2 acute toxicity following preoperative RT. An unacceptable proportion is considered if acute toxicity is observed in 50% or more of the patients. If, during the study duration, more than 50% of the first 10 patients develop ≥grade 2 acute toxicity, the study will be terminated. Therefore, based on the sample size calculation, which ensures that the CI does not encompass an incidence of 50%, a statistical power of 80% and a two-sided alpha of 0.05, a sample size of 21 patients is determined. Adjusting for a 15% allowance to accommodate patients deemed ineligible, the total required sample size is 25.

The assessment of the proportion of patients experiencing ≥grade 2 acute toxicity will be evaluated, and a 95% CI will be calculated. Grade 1 acute and late treatment-induced toxicity, PROMs and cosmetic results will be compared with baseline using linear mixed models for repeated measures. Radiological and pathological response, mastectomy rate, patient comfort during RT treatment delivery and oncological outcomes will be presented using descriptive statistics. The Kaplan-Meier method will be employed to quantify disease-free, breast cancer-specific and OS. Baseline T-cell levels will be analysed across patients to assess interpatient variability and intrapatient changes between baseline and post-treatment timepoints. Overlap in variance among different response markers will be explored. Additionally, the reproducibility of potential response markers, if applicable, will be investigated.

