The presence of the tumour is in situ during PBI, allowing for more precise delineation of target volumes and reduced interobserver variability.^13 29^ Both factors result in smaller irradiated volumes, which allow a higher prescribed dose to be delivered on the tumour in a reduced number of fractions, potentially lowering radiation-associated toxicity and improving cosmetic results.

A recent systematic review of studies on preoperative PBI in primary breast cancer showed that acute toxicity resulting from preoperative RT primarily manifests as grade 1 (19–34%), grade 2 (0–10%) skin toxicity; no grade 3 or higher was reported. The most common late toxicities are fibrosis grade 1 (56–100%) and 2 (9%), breast discomfort/pain grade 1 (13–58%) and 2 (6–13%) and breast oedema grade 1 (31%).^12^ Cosmetic outcomes were assessed as good or excellent by 78–100% of the patients. Concerns have been raised regarding the increased risk of surgical complications after preoperative RT. However, recent studies suggest that a short interval between RT and BCS does not necessarily increase postoperative complications.^12^ In the SIGNAL trial, only 1/52 patients experienced a wound infection after single-dose preoperative PBI followed by BCS after 1 week.^30^ In addition, single-dose preoperative PBI reduces treatment burden for patients and streamlines healthcare logistics in comparison to multiple (ie, 5–23) postoperative re-PBI fractions. Furthermore, it is more cost-effective and sustainable by minimising visits and potentially decreasing side effects and subsequent treatments, thereby lowering overall healthcare costs. This preoperative approach could, after proven effectiveness and limited toxicity, be extrapolated to second BCT in patients with an IRBE with low-risk characteristics.

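### Linear mixed models are prescribed for graded toxicity and four-category physician cosmesis; with 21–25 patients the intervals for sparse toxicity items can be unreliable

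*Protocol article*

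**What the plan says.** The analysis sentence is in the Statistical analysis section: "Grade 1 acute and late treatment-induced toxicity, PROMs and cosmetic results will be compared with baseline using linear mixed models for repeated measures". It names one model family for the whole list.

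The Study outcomes section shows that the list mixes scales:

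- **Toxicity:** "Secondary endpoints are any acute (including grade 1) and late treatment-induced toxicity according to CTCAE V.5.0 and the Clavien-Dindo classification". These are ordered grades.
- **Physician cosmesis:** "The physician will score cosmetic outcome as excellent, good, fair or poor based on changes in breast appearance". These are four ordered categories.
- **Patient-rated cosmesis:** "Cosmetic outcome will be assessed by the patients using the BREAST-Q questionnaire".
- **Objective cosmesis:** "digital photographs analysed by the BCCT.core software and 3D Vectra XT software".

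A baseline value exists for each of these: "At baseline (prior to RT) and prior to BCS, toxicity, PROMs and cosmetic outcome will be assessed". Table 1 restricts baseline late toxicity: "No or mild late toxicity (no grade 2 or higher) from previous breast-conserving therapy". It also excludes patients with a poor cosmetic result after the first treatment.

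The acute secondary endpoint is not worded consistently. Study outcomes covers any acute toxicity, grade 1 included. The Abstract and the Statistical analysis section speak of grade 1 only.

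**The concern.** A linear mixed model assumes roughly normal residuals and treats the distance between neighbouring categories as equal. That can be reasonable for questionnaire and software scores. It fits toxicity grades less well, because most patients may sit at grade 0 and the spread changes between visits.

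The design accentuates this. Baseline precedes radiotherapy, so acute toxicity from the study treatment should be absent or nearly so, and late toxicity can only be grade 0 or 1. Variance is therefore small at baseline and larger later. A random-intercept model with one residual variance averages over that difference. An unstructured model follows it, but produces a zero standard error when no patient changes.

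The article presents its outcome set as evidence on safety, so readers will take these intervals as statements about harm. Intervals that are too narrow, or that extend below 0%, would misstate what 21 to 25 patients can show. This is a method the article states, not a detail left open, so an analysis plan that followed the sentence would inherit the problem.

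**Working it through.** **Inputs from the article.** 21 evaluable patients and 25 in total (21/0.85 = 24.7, rounded up to 25). The article gives no numerical result for these secondary analyses, so there is no figure of its own to reproduce. Its Discussion reports, for primary breast cancer, that "acute toxicity resulting from preoperative RT primarily manifests as grade 1 (19–34%), grade 2 (0–10%) skin toxicity", late grade 2 fibrosis in 9%, late grade 2 breast pain in 6–13% and wound infection in 1 of 52 (1.9%). Some outcomes are therefore sparse. Others are common: late grade 1 fibrosis is put at 56–100%.

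**Assumptions.** Visit-specific rates as shown below, five visits including baseline, complete data and latent within-patient correlation 0.5. Items are analysed one by one, which the article does not specify.

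**Formulas.** With complete data, the contrast between a visit and baseline is the mean paired difference d̄.

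- Unstructured covariance: d̄ ± t(n−1) · SD(d)/√n.
- Random intercept: d̄ ± t((n−1)(k−1)) · √(2s²/n), where s² is the residual variance pooled over the k visits.

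**Simulated coverage of the nominal 95% interval for change from baseline (5,000 runs).**

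| Assumed rates, baseline then later visits | N | Unstructured | Random intercept |
|---|---|---|---|
| 2/9/9/6/6% | 21 | 76–82% | 94–97% |
| 2/9/9/6/6% | 25 | 80–88% | 95–98% |
| 5/10/5/5/5%, at the 10% visit | 21 and 25 | 87–88% | about 91% |
| 10/34/34/20/10% | 21 and 25 | 92–98% | 94–99% |
| 30/50/60/60/60% | 21 and 25 | 95–96% | 95% |
| Four-level score coded 1–4 (three follow-up visits) | 25 | 95% | 95–96% |

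**A baseline of zero.** Take assumed rates 0/5/34/19/5%, N = 25, 20,000 runs. With a random intercept, coverage is 89% at the 34% visit and 99.9% at the 5% visits: too narrow at the peak, too wide elsewhere. With an unstructured covariance, coverage at the 5% visits is about 72%, which can be checked by hand. The chance that no patient has an event is 0.95^25 = 0.277. All differences are then zero, the interval has zero width and it misses the true 5%. Coverage cannot exceed 1 − 0.277 = 72%. With 21 patients the same arithmetic gives 0.95^21 = 0.341 and a ceiling of 66%.

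**Degenerate and impossible results.** In the two low-rate scenarios of the table (first three rows), at least one contrast had zero variance in 31–49% of trials. When some visit had a rate of 10% or less, at least one fitted visit-mean interval left the 0–100% range in 98–100% of trials. When all rates lay between 30% and 60%, this happened in 15–30%.

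**Four-level cosmesis.** Interval coverage holds. What remains is that coding 1 to 4 makes a step from excellent to good count the same as one from fair to poor, so a mean change is hard to interpret.

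**The case against.** The strongest reply has four parts.

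1. **Much of the list suits the model.** Questionnaires, BREAST-Q and continuous photographic measures can reasonably be analysed this way. This stands, and the fix keeps the model for them.
2. **No covariance structure is fixed, and that choice belongs in an analysis plan.** This also stands, so one cannot say which failure would occur. But both usual choices were checked and each has trouble with sparse items, in different ways. The choice of a linear model is itself stated.
3. **The planned quantity is change from baseline, not visit rates.** Fair: negative limits for visit rates matter only if such rates are reported from the model. The undercoverage above is for change from baseline, so that part is not answered.
4. **Nothing decisive depends on it.** The primary endpoint is a proportion with a 95% interval, and the early termination rule uses grade 2 or higher. This stands and limits the weight of the point.

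A reader might also infer that the model could score worsening as improvement, because a patient moving from grade 1 to grade 2 would leave a grade 1 indicator. The documents do not support this as a general claim. It requires coding grade 1 as exactly grade 1, which is nowhere stated and which the wording in Study outcomes argues against. It also requires frequent grade 1 at baseline. With an assumed 40% grade 1 at baseline and 40/30/30% in grades 0/1/2+ later, the exact-grade-1 rate changes by 30 − 40 = −10 points, while grade 1 or higher rises by 60 − 40 = 20 points. With 20% at baseline the indicator rises by 10 points and there is no reversal. Treatment-induced acute toxicity should be near zero at baseline, leaving the indicator little room to fall.

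**Conclusion.** The point holds in a limited form. The article prescribes a linear mixed model for outcomes it defines as ordered categories. For sparse toxicity items, this can give unreliable intervals for change from baseline: about 72–88% coverage with an unstructured covariance in the scenarios simulated (with a ceiling of 66% at 21 patients in the zero-baseline case), and from about 89% to above 99% with a random intercept. These figures rest on assumed rates and correlation, complete data and item-by-item analysis; pooling items would make events less sparse.

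A reader might conclude that all the toxicity and cosmesis intervals are invalid. That goes too far: coverage is about 95% when rates are 30–60%, and 95–96% for a four-level score. For physician cosmesis the objection concerns equal spacing and interpretation only. The primary endpoint and the stopping rule are untouched.

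**What to change.** Amend the analysis sentence as follows.

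- **Linear mixed models:** keep them for PROMs, BREAST-Q and continuous photographic scores only.
- **Toxicity:** report the worst grade per patient and the proportions with grade ≥1 and grade ≥2, separately for acute and late toxicity, with exact 95% intervals. With 0 events in 25, for example, the exact upper limit is 1 − 0.025^(1/25) = 13.7%, not a zero-width interval.
- **Change from baseline in toxicity grade and physician cosmesis:** use a paired categorical method, such as exact McNemar on a stated dichotomy, or an ordinal model where events are frequent enough. Otherwise give descriptive shift tables.
- **Wording:** in the Abstract and the Statistical analysis section, call the acute secondary endpoint any grade (≥1), to agree with Study outcomes. This also removes the exact-grade-1 reading.

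The change is to analysis wording only; it needs no new data and no change in sample size. It costs slightly more analysis work. Paired tests drop patients with an incomplete pair, which matters over five years of follow-up, and ordinal models are themselves fragile with few events, which is why shift tables are the fallback.

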## Discussion

The REPEAT trial aims to investigate the feasibility of second BCT with preoperative PBI among patients with a low-risk IRBE. The feasibility will be assessed based on the incidence of grade 2 or higher acute toxicity induced by RT and surgery. Additionally, the trial will assess PROMs, cosmetic outcomes, oncological endpoints and RT-associated (immuno) biomarkers in both blood and tumour tissue.

Numerous randomised controlled trials (RCTs) have compared BCT and mastectomy, demonstrating similar oncological outcomes in primary breast cancer.^19^ In addition to the excellent survival and recurrence rates, BCT offers an advantage in terms of QoL.^20^,^22^ Patient undergoing BCT have reported improved body image, future perspectives, psychosocial and sexual well-being, with these improvements showing a gradual increase over time.^20^,^22^ It is therefore obvious to consider a second BCT instead of a standard salvage mastectomy in the event of a local recurrence. Advancements in RT techniques over the last decades, such as CT-guided and MR-guided RT and (ultra-) hypofractionation, allow more precise treatment delivery and a lower total dose, respectively, resulting in reduced toxicity. Consequently, the interest in second BCT is increasing.^23^ A systematic review conducted by Walstra *et al* showed that second BCT is feasible.^9^ The weighted estimates for grade 3 and 4 toxicity were 11% for WBI, 9% for external-beam PBI, 9% for interstitial brachytherapy and 18% for intraoperative radiation therapy (IORT). These results suggest a low incidence of adverse events comparable to postoperative RT.^5 9 24^ The cosmetic results were excellent or good in 29–100% of the patients.^9^ Furthermore, patients reported significantly better QoL scores for body image and overall QoL after second BCT compared with those treated with salvage mastectomy. However, data on toxicity, cosmetic outcome and QoL after second BCT were limited, and all available data on second BCT are from retrospective cohort studies. In contrast to primary breast cancer, no RCTs have been conducted comparing second BCT with mastectomy in patients with IRBE, due to the low incidence rate.

The majority of studies investigating reirradiation after BCS primarily focus on brachytherapy.^9^ Additionally, in previous studies on second BCT, whole breast reirradiation was more commonly investigated compared with PBI. In contrast to the primary setting, no RCTs have been conducted to date comparing re-WBI and re-PBI. Re-PBI is increasingly recognised for its benefits, as the localised treatment reduces radiation exposure to the whole breast and associated side effects.^9^ The recent study of Hannoun-Levi *et al* indicates that re-PBI can effectively manage recurrences with acceptable toxicity profiles, further supporting its feasibility in clinical settings.^6^

The selection criteria for patients eligible for second BCT are critical for optimising outcomes. Previous studies provide valuable guidelines for selecting patients suitable for second BCT, emphasising the importance of the interval since the initial treatment.^6 10 25^ There is no consensus on the optimal timing or interval between the primary tumour and recurrence. A shorter interval to the first recurrence is associated with a higher risk of subsequent local and distant recurrences. The eligibility criteria from Gentilini *et al* are tumour size ≤2 cm, a clinically negative axilla, any age and candidates to receive BCT.^25^ These criteria help in identifying patients who are most likely to benefit from second BCT; however, prospective studies are warranted. In addition, understanding the prognostic differences between true recurrences and second primary tumours is crucial for tailoring treatment. Studies suggest that true recurrences generally have a worse prognosis compared with second primary tumours. The recently developed Groupe Européen de Curiethérapie-European Society for Therapeutic Radiology and Oncology TAM score (score based on the combination of time interval between first and second breast surgery [T] and accelerated PBI [A] and molecular [M] classifications) could aid in the decision-making process for a second BCT.^6^ Moreover, tumour-infiltrating lymphocytes (TILs) and circulating tumour DNA (ctDNA) could provide prognostic insights into outcomes.^26^,^28^ RT can modulate the immune response as measured in TILs.^28^ Elevated ctDNA levels post RT could indicate a higher risk of recurrence, providing a valuable biomarker for prognosis.^26 27^ However, data on the value of TILs and ctDNA in patients treated with RT are scarce and require further investigation.

The presence of the tumour is in situ during PBI, allowing for more precise delineation of target volumes and reduced interobserver variability.^13 29^ Both factors result in smaller irradiated volumes, which allow a higher prescribed dose to be delivered on the tumour in a reduced number of fractions, potentially lowering radiation-associated toxicity and improving cosmetic results.

A recent systematic review of studies on preoperative PBI in primary breast cancer showed that acute toxicity resulting from preoperative RT primarily manifests as grade 1 (19–34%), grade 2 (0–10%) skin toxicity; no grade 3 or higher was reported. The most common late toxicities are fibrosis grade 1 (56–100%) and 2 (9%), breast discomfort/pain grade 1 (13–58%) and 2 (6–13%) and breast oedema grade 1 (31%).^12^ Cosmetic outcomes were assessed as good or excellent by 78–100% of the patients. Concerns have been raised regarding the increased risk of surgical complications after preoperative RT. However, recent studies suggest that a short interval between RT and BCS does not necessarily increase postoperative complications.^12^ In the SIGNAL trial, only 1/52 patients experienced a wound infection after single-dose preoperative PBI followed by BCS after 1 week.^30^ In addition, single-dose preoperative PBI reduces treatment burden for patients and streamlines healthcare logistics in comparison to multiple (ie, 5–23) postoperative re-PBI fractions. Furthermore, it is more cost-effective and sustainable by minimising visits and potentially decreasing side effects and subsequent treatments, thereby lowering overall healthcare costs. This preoperative approach could, after proven effectiveness and limited toxicity, be extrapolated to second BCT in patients with an IRBE with low-risk characteristics.

The value of a repeat sentinel lymph node biopsy (SLNB) as a staging tool in patients with an IRBE is disputable. The risk of axillary lymph node metastasis in patients with an IRBE after previous BCS and SLNB is 26%.^31^ A meta-analysis showed that a repeat SLNB has a negative predictive value of 96.5% and a false negative rate of 4.1% for tumour negative nodes.^32^ In the SNARB study, 515 patients with an IRBE underwent repeat SLNB for axillary staging after a median recurrence interval of 10.5 years (0.4–31.8).^33^ In the primary setting, 203 (39.4%) patients underwent an SLNB and 278 (54%) underwent axillary lymph node dissection. The repeat SLNB could not identify the sentinel node in 239 (46.4%) patients.^33^ No significant difference was found in the 5-year recurrence-free survival between patients with an unsuccessful, tumour-positive or tumour-negative SLNB (p=0.543).^33^ Additionally, a recent retrospective cohort of 119 patients with an IRBE with negative lymph nodes on 18F-FDG-PET/CT who underwent repeat SLNB showed that repeat SLNB was successful in 66% of the patients and 8% had a tumour-positive sentinel node.^34^ The 10-year OS was comparable across patients with tumour-positive, tumour-negative and unsuccessful repeat SLNB (89% vs 89% vs 95%, p=0.701). Consequently, in the REPEAT study, a multidisciplinary tumour board will determine the axillary staging method. This also simplifies the treatment process with preoperative PBI and could reduce SLNB-associated morbidities.

Possible limitations of this prospective multicentre study are the relatively short follow-up. The reason for the 5-year follow-up is because of the primary outcome acute toxicity and the feasibility design of this study. Second, the interval between RT and surgery is too short to achieve a pathological complete response. Results from the ABLATIVE trial showed that the rate of PCR is higher after 8 months (48%) compared with 6 months (33%).^14^ This suggests, although patient numbers were small, that the RT may still kill tumour cells after 6 months. To ensure oncological safety in these patients with recurrent breast cancer, we chose an interval of 3 weeks for this feasibility study.
